## Background

The safety of long-acting β_2_-agonists (LABAs) remains controversial in asthma, particularly in children, which led regulators to contraindicate LABAs as a single agent in asthma treatment.^1^ Current evidence regarding the safety of LABAs in combination with inhaled corticosteroids (ICs), based on meta-analyses of randomised clinical trials (RCTs), is less consistent. Recently updated meta-analyses for formoterol and salmeterol failed to reassure on safety.^2,3^ Despite the absence of evidence of serious risk with LABAs associated with ICs, the precision of results was low owing to infrequent outcomes. Furthermore, RCTs include highly selected populations, and they are not properly designed to assess infrequent and/or long-term adverse events in actual conditions of drug use.^4^

Evidence is also limited in the observational context. A recent systematic review assessing the risk of LABAs associated with ICs, compared with ICs alone, did not indicate any increased risk for emergency visits or hospital admissions.^5^ However, no reliable conclusions could be drawn neither in children, nor on potential differences between LABAs associated with ICs, in fixed-dose combinations, and in two separate canisters, due to the lack of published data for these specific issues. This review also highlighted the scarcity of prospective studies and the lack of data on drug adherence. Most of the observational studies were based on claims databases, providing only a partial assessment of drug exposure. There is an evidence gap, as detailed and valid exposure data are needed. For instance, irregular use of ICs in persistent asthma is a well-known source of exacerbations.^6^ Thus, there is a need to explore potential risks associated with LABAs in real life, with more extensive assessments of patterns of use, including ICs concomitant therapy, asthma control and exacerbations over time.

## Aims

The ASTRO-LAB project aims to provide new evidence about the safety of LABAs in children and adults in routine clinical care. Its main objective is to investigate with prospective data whether asthma patients receiving LABAs are at a higher risk of severe asthma exacerbations (SAEx), taking into account baseline differences in severity. Potential variations of respective drug exposures to LABAs and ICs over time, using complementary data sources will also be investigated. In addition, it will be verified whether differential adherence to LABAs and to ICs is a possible mechanism of increased risk of SAEx and other asthma outcomes in patients using these drugs in two separate canisters. A key question that ASTRO-LAB aims to explore is whether the potential LABA-associated risk can be explained by suboptimal adherence to ICs.

## Methods

ASTRO-LAB is a 24-month prospective observational study in asthma, conducted in France and in the United Kingdom (UK).

### Participants

ASTRO-LAB will include persistent asthma patients treated in primary care, equally distributed between children (6–17 years) and adults (18–40 years). Inclusion of patients will be performed between May 2013 and February 2015 in the three steps described hereunder (Figure 1).

#### Patient pre-selection

British patients aged 6–40 years with at least one LABA and/or IC prescription during the past 12 months will be pre-selected from The Health Improvement Network, which is a collection of pseudo-anonymised electronic primary care medical records^7^ collected in approximately 550 general practices in the UK, with 3.6 million active patients.

In France, more than 700 general practitioners will perform a preliminary selection of asthma patients aged 6–40 years, with at least two prescriptions of LABAs and/or ICs during the past 12 months, regardless of associations with other controllers. General practitioners will record all asthma-related prescriptions during the past 12 months. A similar pre-selection will be conducted in community pharmacies: pharmacists will record all asthma-related prescriptions available during this time interval for patients aged 6–40 years, with at least one dispensing of LABAs and/or ICs and two pharmacy visits during these past 12 months.

#### Patient eligibility

From the pre-selection database, the research team will select, in both countries, patients on the basis of an additional inclusion criterion, i.e., ⩾6 months of prescribed coverage of one of the following therapy patterns during the past 12 months: ICs without LABAs, LABAs without ICs, LABAs and ICs as separate inhalers (LABAs+ICs) or fixed-dose combinations (figures available in the Supplementary Information). No change of therapy pattern will be allowed during the last 12 months.

The following exclusion criteria will be checked in pre-selection databases (for the UK) or during enrolment visit by a general practitioner or a pharmacist (for France): chronic oral corticosteroid use (⩾15 consecutive days during the past 3 months), history of omalizumab therapy and/or any other concomitant respiratory disease (chronic obstructive pulmonary disease, cystic fibrosis, pulmonary fibrosis, bronchiectasis and tuberculosis). In case of SAEx within 2 months before inclusion, patients will be re-contacted 4 months later, so that they will be free of recent SAEx when entering the cohort.

#### Patients’ enrolment

In France, general practitioners and pharmacists will invite eligible patients to participate in the study during a general practitioner or pharmacy visit. In the UK, practices will forward postal invitation packs to eligible patients, who will be invited to contact the logistic centre by phone or online. A consent acknowledgement will be collected before any data collection.

### Data collection

Data collection schedule for patient-, caregiver- and health care professionals (HCP)-reported data is summarised in Figure 2.

#### Patient-reported data

##### Computerised-assisted telephone interviews and text messages

Trained interviewers will administer computerised-assisted telephone interviews (CATIs) to patients aged 12–40 years (parents/caregivers of patients aged 6–11 years) immediately after inclusion and every 4 months, to assess asthma control, asthma medication used during the past 4 months and SAEx occurrence. If a SAEx is reported, the asthma control- and medication-related questions will be repeated for the period before the SAEx, followed by additional questions (triggers, management). Patients will also receive monthly text messages inquiring about potential new SAEx; a positive answer will be followed by an additional CATI including the above-mentioned SAEx-related questions.

##### Online surveys

Patients and/or parents/caregivers will be requested to complete online surveys (adapted to age-specific requirements) at 12-month intervals on determinants of medication adherence, self-monitoring of symptoms, triggers and exacerbations management, quality of inhaler technique, quality of life, demographic and other background characteristics.

#### HCP-reported data

HCPs will complete online surveys on their routine asthma care and determinants of adherence support.

#### Electronic medical records/claims data

The Health Improvement Network data will be available in the UK, whereas refill and hospitalisation data will be obtained from the National Health Insurance System (SNIIRAM) in France.

### Measures

We present the main characteristics of the measures relevant to the primary research question regarding the safety of LABAs.

#### Outcomes

The primary outcome will be the occurrence of SAEx,^8–10^ operationalised as occurrence of patient-reported courses of oral corticosteroids (⩾3- day duration), unscheduled asthma-related medical contacts, emergency room visits, hospital admissions and death.

The secondary outcomes will be asthma control, measured with validated questionnaires—symptoms only Asthma Control Questionnaire (ACQ-5)^11^ and the Royal College of Physicians three questions,^12,13^ as well as the five-level European Quality of Life—5 Dimensions (http://www.euroqol.org/about-eq-5d/publications.html (25 November 2013)). For the latter, French and UK valuation set will be applied to estimate utilities in French and English participants, respectively.

#### Medication use and adherence

Medication use will be assessed via CATIs for each daily inhaled medication separately, with questions referring to different time intervals and behaviours: number of doses used the day before the interview, number of days with 0% and 100% adherence during the previous 7 days, number of days of non-use during the previous 4 weeks, treatment interruptions longer than a week in the previous 4 months, and medication overuse (for a specific time interval or occasional) in the previous 4 months. Patient/caregiver-reported drug exposure and adherence will be computed via algorithms developed in preliminary analyses.

### Therapy patterns, sample size and planned analyses

Studied exposure groups will be based on four initial therapy patterns. Preliminary results on pre-selected populations revealed that, for instance, only 2.4% of patients were prescribed LABAs without ICs in France, and virtually none in the UK. Given these low frequencies, patients under LABA monotherapy would be merged with those receiving ICs and LABAs as separate canisters, after having preliminarily verified their comparability. Hence, three groups have been considered for sample size power computation: LABAs with ICs in separate canisters or in monotherapy, LABA/ICs fixed-dose combinations and ICs without LABAs.

#### Sample size

Sample size computation for required power was based on differences in binomial proportions of SAEx between the reference ICs without LABAs group and LABAs with ICs in separate canisters or in monotherapy group. The hypothesis for the outcome frequency (24%) was based on asthma-related oral corticosteroid courses reported by patients during a 12-month period in a pharmacy-based study conducted in 2007 in ICs-treated patients.^14^ This hypothesis is conservative, as it may underestimate the true frequency of SAEx, which not only consider oral corticosteroid courses but also hospitalisations, unplanned medical contacts and death. Sample size calculations were based on the expected 1.3-fold higher frequency SAEx between the ICs without LABAs group and the other two groups. Considering a bilateral approach and balanced counts between groups, it was calculated that a total of 2,200 patients would be required given a statistical power of 80%, at a significance level of 5%, with a potential 20% loss to follow-up.

#### Planned analyses

##### Safety analyses

*Between-group comparisons*. As first approach, the time to the occurrence of the first SAEx will be compared between the initial exposure groups (ICs without LABAs group as reference) with survival analyses (Kaplan–Meier, Cox Model). The total number of SAEx per patient during a 12-month period will be also compared using Poisson regression.

*Cohort analyses with time-dependent variables*. Patients’ actual exposure to LABAs and ICs may change over follow-up owing to the prescriber or patient. In these analyses, such changes will be taken into account. Time-dependent variables, reflecting LABAs or ICs exposure over follow-up, will be constructed. The association between exposure to LABAs over time and the occurrence of SAEx will be investigated, after adjusting in particular for concomitant exposure to ICs. Survival analyses and hierarchical longitudinal models will be applied. Different markers of drug exposure and adherence will be successively explored.

*Case–crossover study and nested case–control study approaches*. As in a case–crossover design patients are their own controls, LABAs and ICs studied drug exposure patterns occurring just before a SAEx (case period) will be compared with those observed during a preceding regular CATI with no SAEx reported (control period), thus eliminating any potential influence of patients fixed characteristics. A nested case–control study approach will be also considered.

*Adjustment for asthma baseline severity*. Analyses will be adjusted for the different markers of asthma baseline severity, as it is a potential confounding factor when assessing LABA-related risk, except for the case–crossover approach.

Complementary analyses will be considered with the French patients, using claims data.

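### Per-patient SAEx totals are to be compared by Poisson regression with no stated allowance for overdispersion, so the standard errors of this additional comparison are likely to be too small

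*Protocol article*

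**What the plan says.** The Protocol article, Safety analyses, gives two between-group comparisons by initial therapy pattern. The leading one is a survival analysis: "As first approach, the time to the occurrence of the first SAEx will be compared between the initial exposure groups". The second is a count analysis: "The total number of SAEx per patient during a 12-month period will be also compared using Poisson regression". Poisson regression is the only count model named in the article. Overdispersion, robust or scaled variance, and an offset for incomplete follow-up are not mentioned.

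The surrounding text matters for the reach of the point:

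- Covariates: "Analyses will be adjusted for the different markers of asthma baseline severity", with only the case-crossover approach excepted.
- Time-dependent exposure analyses: "Survival analyses and hierarchical longitudinal models will be applied".
- Event collection allows repeat events per patient. Interviews take place every 4 months, and "Patients will also receive monthly text messages inquiring about potential new SAEx".
- The Sample size section allows for incomplete follow-up: "with a potential 20% loss to follow-up".
- The Methods section states: "ASTRO-LAB is a 24-month prospective observational study in asthma".

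**The concern.** A Poisson model with model-based standard errors takes the variance of each patient's count to equal its mean, given the covariates. That fails when some patients are persistently more prone to exacerbations than the covariates explain. The article itself gives reason to expect this. The Background names irregular use of inhaled corticosteroids as a known cause of exacerbations, and the Adherence analyses treat varying adherence as a main subject. Adjustment for baseline severity would not remove differences in adherence.

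With overdispersed counts the rate ratio can still be estimated, but its confidence interval is too narrow and its test rejects too often. In a study of a disputed safety signal, this comparison could then show an apparent LABA-related difference in event totals at more than the nominal error rate.

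A smaller related matter is that a total over a fixed 12 months needs a rule for patients observed for less than 12 months. The sentence gives none.

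**Working it through.** **1. The plan's own figure.** Inputs from the Sample size and Therapy patterns sections: 24% in the reference group, 1.3-fold increase (0.24 × 1.3 = 31.2%), two-sided 5%, 80% power, three balanced groups, 20% loss.

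n per group = [1.960·√(2·0.276·0.724) + 0.842·√(0.24·0.76 + 0.312·0.688)]² / 0.072² = 604.

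- Dividing by 0.8 gives 755 per group, 2,265 in total.
- Multiplying by 1.2 gives 725 per group, 2,175 in total.

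Both are within 3% of the stated 2,200. The calculation rests on binomial proportions, so the choice of count model does not affect it.

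**2. Inputs for the count analysis.**

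- 12-month probability of at least one event: 24% (Sample size).
- Evaluable patients per group: 2,200 × 0.8 / 3 = 587.
- Dispersion k: not in the document. It is assumed to be 0, 0.5, 1 or 2, and stands for what remains after covariate adjustment.

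**3. Formulas.** Take negative binomial counts with mean μ and variance μ(1 + kμ). The probability of no event is (1 + kμ)^(−1/k). Setting this to 0.76 gives 1 + kμ = 0.76^(−k), and hence μ. For k = 0, μ = −ln 0.76 = 0.274.

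With equal rates in the two groups:

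- Poisson SE / true SE = 1/√(1 + kμ)
- True size of the nominal 5% test = 2·[1 − Φ(1.96/√(1 + kμ))]

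**4. Results.** The simulations used 20,000 replicates per k, with 587 patients per group.

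| k | μ | 1 + kμ | Poisson SE / true SE | SE too small by | True size | Simulated, Poisson SE | Simulated, sandwich SE |
|---|---|---|---|---|---|---|---|
| 0 | 0.274 | 1.000 | 1.00 | 0% | 5.0% | not run | not run |
| 0.5 | 0.294 | 1.147 | 0.934 | 7% | 6.7% | 6.9% | 5.3% |
| 1 | 0.316 | 1.316 | 0.872 | 13% | 8.8% | 8.5% | 4.9% |
| 2 | 0.366 | 1.731 | 0.760 | 24% | 13.6% | 13.3% | 5.1% |

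If the true rate ratio is 1.3 rather than 1, the Poisson SEs are 7%, 14% and 26% too small for k = 0.5, 1 and 2.

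**5. Would a longer window alone help?** No. With 24 months per patient the inflation factor becomes 1 + 2kμ, that is 1.294, 1.632 and 2.463. The size of an uncorrected Poisson test then rises to about 8.5%, 12.5% and 21%. The variance has to be corrected whatever the window.

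**The case against.** The strongest reply is that the sentence neither states nor excludes a robust or scaled variance, and that a condensed article may leave such detail to the full protocol or analysis plan. An offset is likewise a routine part of Poisson regression. The size of the error depends wholly on an assumed dispersion: it is nil at k = 0 and modest at k = 0.5, and the planned severity adjustment may absorb part of the heterogeneity. All of this stands as a limit on certainty. It does not remove the point, because the article names the model, and that model is reliable here only with a correction that it does not mention.

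A reader might infer three stronger things that the document does not support.

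- **That the second year of data is thrown away.** The 12-month period applies to this one count comparison. The Kaplan–Meier and Cox analyses and the time-dependent analyses carry no such cut. The window also matches the 12-month basis of the 24% used for the sample size, and it limits drift away from the initial exposure group. It is a trade-off. Follow-up per patient is not stated outright, and "Inclusion of patients will be performed between May 2013 and February 2015", so the amount of unused follow-up cannot be fixed from the text.
- **That loss to follow-up biases the rate ratio.** Only an overall potential loss of 20% is given. Nothing indicates unequal loss between groups, and the article does not say that patients with partial follow-up are dropped or counted as complete.
- **That the study's main safety conclusion is compromised.** The count comparison is introduced as an addition to the time-to-first-event analysis, which does not depend on the count model.

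**Conclusion.** The point holds for the count comparison. Poisson regression is the only model named for a recurrent event whose risk is likely to vary between patients, and no protection against overdispersion is stated. For an assumed residual dispersion of 0.5 to 2, with 24% of patients having an event in 12 months, standard errors are about 7% to 24% too small and the true size of a nominal 5% test is about 6.7% to 13.6%. With no residual dispersion there is no error. For a given dispersion the problem grows with event frequency, and the Sample size section itself says that 24% may be an underestimate.

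This should be fixed, but it is not critical. It concerns an additional between-group comparison and leaves the sample size, the time-to-first-event analysis and the time-dependent analyses untouched.

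**What to change.** In the between-group comparisons under Safety analyses, replace Poisson regression by negative binomial regression, or by Poisson regression with robust (sandwich) standard errors. Include log observed follow-up time within the 12-month period as offset, so that patients lost before 12 months contribute the time for which they were observed. Keep the baseline severity adjustment already planned.

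The 12-month window may stay. A count over all available follow-up can be added as a sensitivity analysis, with the same model and offset.

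The cost is one sentence and no new data. Confidence intervals will be somewhat wider. With equal rates, the standard error relative to uncorrected Poisson rises by factors of 1/0.934 = 1.07, 1/0.872 = 1.15 and 1/0.760 = 1.32 for dispersion 0.5, 1 and 2. If the counts turn out not to be overdispersed, almost nothing is lost.

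### The case-crossover case period, placed just before a SAEx that is defined mainly by the care it triggers, can take in inhaler use that responds to the attack

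*Protocol article*

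**What the plan says.** The Protocol article, under Safety analyses, describes a case-crossover comparison of "drug exposure patterns occurring just before a SAEx (case period") with "those observed during a preceding regular CATI with no SAEx reported (control period"). The benefit it claims for self-matching is removal of the influence of fixed patient characteristics. Adjustment for baseline severity is not applied to this analysis.

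Under Outcomes, the SAEx is "operationalised as occurrence of patient-reported courses of oral corticosteroids (⩾3- day duration), unscheduled asthma-related medical contacts, emergency room visits, hospital admissions and death".

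Under Computerised-assisted telephone interviews and text messages, when a SAEx is reported, "the asthma control- and medication-related questions will be repeated for the period before the SAEx, followed by additional questions (triggers, management").

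Under Medication use and adherence, the questions include "number of doses used the day before the interview, number of days with 0% and 100% adherence during the previous 7 days". They also cover non-use over 4 weeks, and interruptions of more than a week and overuse (including occasional overuse) over 4 months. Exposure is to be computed by algorithms developed in preliminary analyses.

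Under Adherence analyses, the working hypothesis is that LABA use masks early symptoms while IC adherence is poor, until a severe and sudden SAEx follows.

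**The concern.** Every component of the SAEx except death is a treatment or a contact with care, and these usually come after symptoms have begun to worsen. A window tied to the SAEx can therefore contain the start of the attack itself. Someone who had let an inhaler lapse may take it up again at that point, or use more of it, because of the symptoms. Read as exposure before the event, that use looks like a cause when it is a consequence.

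The control period cannot balance this, because it is chosen for having no SAEx. Matching each patient to themselves does not help either, because the change happens within the patient over time.

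Resumed LABA use would push the LABA odds ratio above 1 with no drug effect. Resumed IC use, on markers that look back only a day or a week, would weaken the sign of an IC lapse. Whether poor IC adherence explains any LABA risk is the question the Aims section singles out, so both distortions touch it.

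**Working it through.** **Passages side by side.** (1) The case period is placed just before the SAEx. (2) The SAEx is dated by care, or by death. (3) Medication use is asked for the period before the SAEx. (4) The additional SAEx questions named are triggers and management; a date of first worsening is not among them. (5) The protocol's own hypothesis assumes symptoms, with LABA use, before the SAEx. Steps 1 to 3 let symptom-driven use enter the case period, and step 5 shows that a symptomatic phase is expected.

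**The protocol's sample size, checked first.** 24% against 24% × 1.3 = 31.2%, two-sided 5%, 80% power, gives 604 per group, or 1,812 for three groups. With 20% loss this is 2,265 (755 per group after dividing by 0.8) or 2,175 (725 per group after multiplying by 1.2). The stated 2,200 lies between them. The concern does not depend on this figure and does not change it.

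**Bias under no true effect.** All inputs here are assumptions, because the document gives none:
- p = 0.7, the probability of LABA use in an ordinary window;
- q, the share of non-users who resume between onset and the SAEx;
- ρ, the within-patient correlation of use between windows.

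Without reactive use, each discordant cell is d = p(1−p)(1−ρ), and the cell unexposed in both windows is u = (1−p) − d. With reactive use:
- exposed in the case window only: b = d + u·q
- exposed in the control window only: c = d(1−q)
- apparent matched OR = b/c

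At q = 0.20:
- ρ = 0: d = 0.21, u = 0.09; OR = 0.228/0.168 = 1.36
- ρ = 0.6: d = 0.084, u = 0.216; OR = 0.1272/0.0672 = 1.89

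| ρ | q = 5% | q = 10% | q = 20% |
|---|---|---|---|
| 0 | 1.08 | 1.16 | 1.36 |
| 0.3 | 1.11 | 1.23 | 1.51 |
| 0.6 | 1.19 | 1.40 | 1.89 |

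Lower ordinary use gives larger values. At p = 0.3 with independent windows the ORs are 1.18, 1.37 and 1.83. If the window ends at onset, q = 0 and the OR is 1.00.

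**Scale of comparison.** The 1.3-fold effect used for sizing is a ratio of proportions. As an odds ratio it is (0.312/0.688)/(0.24/0.76) = 1.44.

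**Chance of a false significant result.** Patients in the ICs-without-LABAs group have no LABA at entry and can rarely form LABA-discordant pairs, so only the two LABA groups are counted: 0.24 × 2,200 × 0.8 × 2/3 ≈ 282 cases over 12 months. With a McNemar test, z = √282·(b−c)/√(b+c). At q = 0.20, b−c = 0.06.
- ρ = 0: z = 16.79 × 0.06/√0.396 = 1.60; probability about 0.36
- ρ = 0.3: z = 16.79 × 0.06/√0.2952 = 1.85; about 0.46
- ρ = 0.6: z = 16.79 × 0.06/√0.1944 = 2.28; about 0.63

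At q = 5–10% the same calculation gives about 0.07 to 0.22, against a nominal 0.05.

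**The case against.** The strongest reply is that this is one sentence in a condensed article. Window length, lag and anchor are commonly left to the full protocol or the analysis plan, and the SAEx interview script is not shown. That stands in part. No section fixes the end of the case period in days, so a reader who infers that the protocol ends it at the moment of care goes beyond the text. What remains is that the article does state an anchor, and followed as written it admits the symptomatic phase.

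Other stronger readings are tempting but not supported:
- *That resumed IC use would hide the IC lapse altogether.* The 4-week non-use and 4-month interruption items would still record a lapse, so only the shortest markers are exposed. The day-before item also refers to the interview, how it is adapted to a SAEx is not stated, and the choice of marker is left to algorithms still to be developed.
- *That moving the window is the only remedy.* Asthma control is also asked for the period before the SAEx and could support a sensitivity analysis, although no such use is stated.
- *That the protocol presents this analysis as free of patient-level confounding.* It claims removal of fixed characteristics only.
- *That the bias matches the effect the study is sized for.* On the odds-ratio scale that effect is 1.44. At p = 0.7 it is not reached at 10% resumption for any correlation examined, nor at 20% with independent windows.
- *That the main safety result is compromised.* The first approach compares groups by initial therapy pattern, which is set before any SAEx in follow-up.

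**Conclusion.** The concern holds for the case-crossover analysis, and for the nested case–control analysis if exposure there is taken up to the SAEx. As described, the case period can include reactive inhaler use that the control period lacks, and the design has no stated means of removing it.

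The size is illustrative only. An apparent LABA odds ratio of 1.08 to 1.89 under no effect rests on an assumed 70% ordinary use, 5–20% resumption and correlation of 0 to 0.6. The false-positive range of 0.36 to 0.63 applies only at 20% resumption, with about 282 cases counted over 12 months; a count over the full 24 months could be higher. At 5–10% resumption the inflation is modest. For ICs the exposure to bias is confined to the short look-backs. This should be corrected because the analysis bears on the study's key question, but it is supplementary and the comparison by initial therapy pattern stands.

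**What to change.** Add one item to the SAEx interview already planned: the date on which symptoms began to worsen. Run the case-crossover with the case window ending at that date. Where it is missing, end the window a prespecified lag before the first steroid dose or contact. Use a control window of the same length.

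Report the just-before-SAEx window beside it rather than dropping it, because the masking hypothesis concerns LABA use during early symptoms. State in advance that a LABA or IC association will be read as drug-related only if it persists in the onset-anchored window. Apply the same lag to the nested case–control analysis if it is run.

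The cost is one interview question and a shifted window in the analysis code; the sample size does not change. The question has to be asked at the time, since an onset date is hard to recover later. Two drawbacks remain: onset dates are recalled, and a drug effect of very short latency would be partly missed. Showing both windows makes the second visible.
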